### Statistical analyses

#### Phase I

Phase I will include a maximum of 18 patients (only non-small-cell lung cancer patients will be included in this step).

6 +/- 3 patients for the sequential scheme evaluation.6 +/- 3 patients for the concomitant scheme evaluation.

As the safety of the anti-TIGIT and anti-PD-L1 combination has been previously validated, we focused the DLTs on radiation-induced toxicities. We chose to accept no more than 22% of radiation-induced toxicities, as patients will undergo additional chemotherapy-related toxicities.

#### Expansion cohorts phase

Depending on the results of toxicity from phase I, a sequential or concomitant scheme will be selected according to decision diagrams.

20 patients will be included in each cohort (including 6 to 9 patients from phase 1 for the lung cancer cohort). Each cohort will be analyzed independently.

20 patients in each cohort will allow for preliminary estimates of efficacy endpoints. A total sample of 18 subjects (assuming 10% of non-evaluable patients) provides a 95% CI with a precision of 22%, 23%, and 24% when the estimated rates of 6-month PFS (under binomial assumption and with no censored data) are 35%, 30%, and 45%, respectively, in head and neck, renal and lung cancers. For head and neck cancer, the 6-month PFS estimate of 35% was selected on the basis of the 6-month PFS rates achieved in Keynote-048 [8], 25% and 45% with pembrolizumab and pembrolizumab plus chemotherapy, respectively. For renal cancer, few data are available on immunotherapy efficacy after a first-line treatment consisting of an immune checkpoint inhibitor combination or an association of a tyrosine kinase inhibitor and immune checkpoint blockade. The chosen 6-month PFS rate is close to what has been observed in the CheckMate-025 [22] study with nivolumab as a second-line treatment. Lastly, for lung cancer, randomized clinical trials of second-line treatment were performed before the use of chemo-immunotherapy as the first-line standard of care [23–26]. In recent retrospective studies assessing chemotherapy in a second-line setting after immunotherapy, the 6-month PFS percentage approaches 40% similarly to the chosen rate [27, 28].

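### The 95% CI precisions quoted for the three planning rates cannot all come from one standard method; the head-and-neck and renal figures appear to be transposed

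*Protocol article*

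**What the plan says.** The text is in the protocol article, Statistical analyses, Expansion cohorts phase. It sets the cohort size first: "20 patients will be included in each cohort". It then moves to the evaluable number and its precision: "A total sample of 18 subjects (assuming 10% of non-evaluable patients) provides a 95% CI". The precisions and rates are given as two parallel lists. A sample of 18 "provides a 95% CI with a precision of 22%, 23%, and 24% when the estimated rates of 6-month PFS" "are 35%, 30%, and 45%, respectively, in head and neck, renal and lung cancers". Read in order, the pairs are:

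- head and neck: rate 35%, precision 22%
- renal: rate 30%, precision 23%
- lung: rate 45%, precision 24%

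The stated basis is "under binomial assumption and with no censored data". The interval method is not named. The same paragraph says separately that 35% is the head-and-neck rate, so the list of rates is in its intended order.

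**The concern.** The two lists run in incompatible orders. For a binomial proportion at fixed n, the variance p(1 − p)/n rises as p moves from 30% to 35%, so the interval at 35% should be the wider one. The article gives the narrower interval to 35% and the wider one to 30%.

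The expansion phase is described as giving preliminary estimates, and the article states no null rate, hypothesis test or power for it. The precisions are therefore its whole quantitative case for 20 patients per cohort. If the figures are transposed, the article slightly overstates the precision for head and neck and slightly understates it for renal.

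**Working it through.** **Inputs (all from the Expansion cohorts phase section)**

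- Enrolled per cohort: 20. Non-evaluable: 10%. Evaluable: 20 × 0.9 = 18, which agrees with the article.
- Rates: 35% (head and neck), 30% (renal), 45% (lung).
- Stated precisions in the same order: 22%, 23%, 24%.
- Model: binomial, no censoring.
- Assumptions: the interval is two-sided (2.5% in each tail), and precision means half-width.

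**Step 1: try to reproduce the printed figures with the Wald interval**

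Half-width = 1.96 × √[p(1 − p)/18]

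- 35%: 1.96 × √(0.2275/18) = 1.96 × 0.1124 = 22.0%
- 30%: 1.96 × √(0.2100/18) = 1.96 × 0.1080 = 21.2%
- 45%: 1.96 × √(0.2475/18) = 1.96 × 0.1173 = 23.0%

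Only the first matches. The Wald maximum at n = 18, reached at 50%, is 1.96 × √(0.25/18) = 23.1%, so this formula cannot give 24% at any rate.

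**Step 2: try the exact (Clopper-Pearson) interval**

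With x = 18p, the lower limit is the 2.5% quantile of Beta(x, 18 − x + 1), the upper limit is the 97.5% quantile of Beta(x + 1, 18 − x), and the half-width is half the difference.

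| Cohort | Rate | x = 18p | Exact interval | Half-width | Rounded | Printed |
|---|---|---|---|---|---|---|
| Head and neck | 35% | 6.3 | 14.5% to 60.6% | 23.1% | 23% | 22% |
| Renal | 30% | 5.4 | 11.1% to 55.7% | 22.3% | 22% | 23% |
| Lung | 45% | 8.1 | 22.0% to 69.7% | 23.9% | 24% | 24% |

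These x values are not whole numbers, so the intervals are interpolations. At the nearest attainable counts (6, 5 and 8 of 18) the half-widths are 22.8%, 21.9% and 23.9%, which also round to 23%, 22% and 24%.

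**Step 3: check whether another method gives the printed order**

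Half-widths at n = 18, for 35% / 30% / 45%:

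| Method | 35% | 30% | 45% |
|---|---|---|---|
| Wald, divisor n − 1 | 22.7% | 21.8% | 23.7% |
| Wald, t quantile | 23.7% | 22.8% | 24.7% |
| Wald, continuity correction | 24.8% | 24.0% | 25.8% |
| Wilson | 20.2% | 19.5% | 20.9% |
| Wilson, continuity correction | 22.4% | 21.8% | 23.1% |
| Agresti-Coull | 20.3% | 19.8% | 20.9% |
| Jeffreys | 20.7% | 20.0% | 21.5% |
| Logit | 20.8% | 20.2% | 21.5% |
| Log-log | 20.7% | 19.8% | 21.8% |

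None rounds to 22 / 23 / 24, and in every row the value at 30% is below the value at 35%. Reading precision as the distance to one limit does not help: the exact upper distances are 25.6%, 25.7% and 24.7%, and the lower distances are 20.5%, 18.9% and 23.0%.

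**Step 4: exchange the first two printed figures**

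The set becomes 23 / 22 / 24, which the exact method reproduces in full. The Wald form with divisor n − 1 rounds to the same three figures. The transposition therefore explains the numbers well, but it does not by itself establish which method was used.

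**The case against.** The strongest reply is that nothing turns on this. Two figures move by about one point, the range quoted across the three cohorts stays 22% to 24%, and the cohort size is unchanged. The results will carry Kaplan-Meier confidence intervals, so the planning figures do not enter the analysis. All of that stands, and it makes this a small correction. It does not make the printed statement right, and no other part of the article repairs it.

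A second reply is that the transposition is not proven. Under the plain Wald formula the head-and-neck figure is correct as printed (22.0%), and renal and lung would be the wrong ones (21.2% and 23.0%). This stands too. It limits what can be said about which figure is wrong, but the printed order fails under either method.

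Two stronger readings are tempting, and the document does not support them.

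- A reader might infer that the bladder cohort has no sample size justification, since no rate or precision is given for it. The sentence names three cancers and says nothing false about the fourth. A planning rate for one cohort is a detail that an article may leave to the full protocol. The exact half-width at n = 18 is in any case at most 24.0% at any rate.
- A reader might infer that the lung planning rate is wrong, because 45% is set beside retrospective data described with the words "the 6-month PFS percentage approaches 40% similarly to the chosen rate". That is loose wording about a judgement, not an arithmetic error. At 40% the exact half-width is 23.6%, which still rounds to 24%.

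**Conclusion.** The concern holds as an error in the printed figures. At n = 18, precisions of 22%, 23% and 24% cannot all belong to rates of 35%, 30% and 45% under one standard binomial method. The most likely explanation is that the head-and-neck and renal figures changed places; the exact method then fits all three.

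The size is about one percentage point for each of two figures if exact intervals were used. If plain Wald was used, renal is too high by 1.8 points (23% against 21.2%) and lung by 1.0 point (24% against 23.0%). The conclusion assumes a two-sided 95% interval, precision read as half-width, and the same 18 evaluable patients in each cohort. It does not show that the cohorts are too small, and it leaves the design and the analysis as they are.

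**What to change.** Confirm which interval method was used, name it in the sentence, and restate the three precisions in the order of the rates. With exact (Clopper-Pearson) binomial intervals at n = 18, these are 23% for head and neck (35%), 22% for renal (30%) and 24% for lung (45%). If the calculation was Wald, they are 22%, 21% and 23%.

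The cost is one corrected sentence. The sample size, the procedures and the analysis do not change.

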#### Definition of study population analysis

The safety population is defined by all patients who received at least 1 dose of immunotherapy combined with at least 1 radiation therapy session.

The modified-intention-to-treat (mITT) population is defined by all patients treated with the phase I recommended scheme who received at least one administration of each immunotherapy, the 3 radiotherapy fractions, and at least one tumor evaluation (CT-scan).

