### Phase I design

Two different schemes of administration will be investigated:

Sequential administration (scheme 1): SBRT (3 fractions of 8 Gy in 5 days) starting on week 1, followed by the first injection of atezolizumab + tiragolumab at week 2, then every 21 days.Concomitant administration (schema 2): SBRT (3 fractions of 8 Gy in 5 days) starting on week 1, with the first injection of atezolizumab + tiragolumab concomitant to the first radiotherapy fraction, then every 21 days.

Immunotherapies will be administered intravenously: atezolizumab (1200 mg) first, then tiragolumab (600 mg) second. The fixed dose of 600 mg was selected on the basis of available clinical pharmacokinetics, efficacy, and safety data from the combined phase Ia/phase I study (GO30103), with single-agent tiragolumab or tiragolumab in combination with atezolizumab. This dose regimen was used in the CITYSCAPE trial that assessed the atezolizumab and tiragolumab combination in metastatic NSCLC [14, 15]. The study design is provided in Fig. 2.

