### Study endpoints

#### Primary end-points of phase I

Safety will be evaluated using DLTs (Dose-Limiting Toxicities) that occur:

the first 5 weeks (35 days) after the first dose of study treatment for **sequential** administration (3x8 Gy of radiotherapy and 3 dosings of immunotherapy)the first 4 weeks (28 days) after the first dose of study treatment for **concomitant** administration (3x8 Gy of radiotherapy and 3 dosings of immunotherapy).

DLTs are defined by all events that are deemed related to the study treatments (SBRT and/or tiragolumab and/or atezolizumab), unless there is a clear alternative cause, with CTCAE version 5.0 grade ≥ 3 non-resolutive (return to basal grade) after 14 days. Any grade 5 related to study treatment will be considered a DLT. No clinical trial has combined SBRT, anti-PD-L1, and anti-TIGIT yet. In order to reduce toxicity risk, we will use a non-ablative SBRT dose, and we will begin this trial by first evaluating tolerance using two types of combination schedules. For the first one, immunotherapies will be administered one week after the start of SBRT with at least 2 days between the end of radiotherapy and the injection of immunotherapy. If no DLT is highlighted, we will evaluate the tolerance of our combination administered using the concomitant scheme. The concomitant scheme was designed on the basis of our preliminary data obtained with RT delivered on the same day as immunotherapy initiation. The decision diagram provided in Fig. 3 describes how the scheme of administration will be selected (sequential or concomitant). If safety is validated with the sequential schedule, the concomitant schedule will be assessed. If safety is then validated with the concomitant schedule, this scheme of administration will be selected for expansion cohorts. Otherwise, the sequential schedule will be selected for expansion cohorts. If there is no difference in toxicity, the concomitant schedule will be selected. Safety is defined according to the decision diagram.

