#### Statistical analysis of endpoints

The primary endpoint will be evaluated in the safety population. Secondary efficacy endpoints will be evaluated in the mITT population, and secondary safety endpoints in the safety population.

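### The safety population requires both an infusion and a radiotherapy session, so a sequential-scheme patient whose SBRT toxicity means no infusion is ever given has a DLT but falls outside the safety tables and, read literally, the DLT evaluation

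*Protocol article*

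**What the plan says.** Under Definition of study population analysis, the safety population is "all patients who received at least 1 dose of immunotherapy combined with at least 1 radiation therapy session". Both components are required. Under Statistical analysis of endpoints, "The primary endpoint will be evaluated in the safety population", with "secondary safety endpoints in the safety population" as well.

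Phase I design separates the two components in the sequential scheme: SBRT "starting on week 1, followed by the first injection of atezolizumab + tiragolumab at week 2". Primary end-points of phase I adds that "immunotherapies will be administered one week after the start of SBRT with at least 2 days between the end of radiotherapy and the injection of" the antibodies. In the concomitant scheme, SBRT starts "with the first injection of atezolizumab + tiragolumab concomitant to the first radiotherapy fraction".

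For the sequential scheme, DLTs are counted over "the first 5 weeks (35 days) after the first dose of study treatment", and the first study treatment there is SBRT. An event qualifies if it is related to SBRT, to either antibody, or to any combination of them. It must be grade 3 or higher and not back to the baseline grade after 14 days; any related grade 5 event counts at once. The Phase I paragraph of the statistical section says that "we focused the DLTs on radiation-induced toxicities".

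Under the decision diagram, a scheme is safe with 0 or 1 DLT in 6 patients, or with 2 in 6 followed by 0 in 3 more.

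**The concern.** The DLT definition and the analysis population do not cover the same patients. The definition follows a sequential patient from the first SBRT fraction and counts harm from SBRT alone. The population admits that patient only once an infusion has been given. Between the two lies a period of SBRT-only exposure. Someone whose radiation toxicity in that period is fatal, or persists and permanently rules out the infusion, has a DLT but never enters the population.

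This differs from ordinary handling of non-evaluable patients, because here the reason for exclusion is the outcome being counted. It also concerns radiation toxicity, the kind on which the article says its DLTs focus. The gap arises mainly in the sequential scheme. That scheme's result opens the concomitant scheme, and sequential is the fallback for the expansion cohorts. If sequential is selected, the same gap carries into the expansion safety tables.

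**Working it through.** **1. Who is lost.** All of the following must hold:

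- The patient received at least one SBRT fraction and no infusion at any time.
- The reason is an SBRT-related event inside the 35-day window.
- The event is grade 5, or grade 3 or higher and unresolved after 14 days.

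Such a patient meets the DLT definition but not the safety population definition. A patient harmed in week 1 and infused later, on time or late, stays in with every event.

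**2. The plan's own figure.** The statistical section accepts at most 22% toxicity. The largest passing result under the decision rule is 2 DLTs in 6 + 3 = 9 patients, and 2/9 = 22.2%. The figure reproduces.

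**3. Sensitivity of the decision to one patient.** Suppose 3 of 6 patients have a DLT (not safe). One is excluded and the replacement has no DLT: the count becomes 2 of 6, and three more patients are entered. In the same way, 2 of 6 becomes 1 of 6, safe without extension. Both steps require that the replacement has no DLT, or that the denominator simply stays at 6.

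**4. Chance of passing with every DLT counted.** With true DLT rate p, exact binomial:

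P(pass) = P(0 or 1 of 6) + P(2 of 6) × (1 − p)³

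At p = 0.30: 0.1176 + 0.3025 + 0.3241 × 0.3430 = 0.531.

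At p = 0.40: 0.0467 + 0.1866 + 0.3110 × 0.2160 = 0.300.

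**5. Chance of passing when some DLT patients are lost.** Let f be the share of DLTs that precede the infusion and permanently prevent it. The article gives no value, so f is an assumption, as is replacement of the excluded patients. The rate among counted patients is then

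p′ = p(1 − f) / (1 − pf)

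For p = 0.30 and f = 0.05: p′ = 0.285 / 0.985 = 0.289.

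| Assumed f | p′ at p = 0.30 | P(pass) | p′ at p = 0.40 | P(pass) |
|---|---|---|---|---|
| 0 | 0.300 | 53.1% | 0.400 | 30.0% |
| 5% | 0.289 | 55.8% | 0.388 | 32.6% |
| 10% | 0.278 | 58.7% | 0.375 | 35.3% |
| 20% | 0.255 | 64.6% | 0.348 | 41.4% |
| 30% | 0.231 | 70.7% | 0.318 | 48.6% |

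If the denominator stays at 6 and the lost DLTs simply go uncounted, p′ = p(1 − f). At p = 0.30 and f = 10% this gives 0.27 and a 60.8% chance of passing, against 58.7% with replacement. The direction is the same under both models.

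**The case against.** Several points on the other side stand.

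- **The group is narrow.** A reader might infer that anyone harmed by SBRT before the week-2 infusion drops out. The documents do not support that: one infusion at any time suffices for inclusion. A week-1 event of grade 3 or 4 is also not a DLT if it resolves within 14 days, and it cannot be classified as one until after the planned infusion date.
- **Loss from the DLT count is not certain.** The decision rule speaks of patients out of 6 and of newly included patients, without naming the safety population. The phase I adverse event listing names no population either. The sentence on the primary endpoint does not say which phase it means, and the secondary endpoints named with it belong to the expansion phase. A never-infused patient might therefore be counted in practice. This does not rescue the wording. The sentence precedes both the phase I and the expansion analyses, and secondary safety endpoints use the restricted population in any case.
- **The size rests on assumptions.** Neither f nor a replacement rule is in the article. The relevant f covers only DLTs that permanently prevent infusion, which cannot exceed the share that merely precede it.
- **A mirror-image loss in the concomitant scheme is not shown.** One might infer that a patient reacting to the day-1 infusion before the first fraction is also lost, but no order within the day is stated.
- **The consequence may be limited.** If the concomitant scheme passes, it is selected and the gap nearly disappears from the expansion cohorts. The IDMC also reviews toxicity for each patient in the three non-lung cohorts.

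**Conclusion.** The point holds in this limited form. As written, the population excludes a sequential patient whose SBRT toxicity means that no infusion is ever given. That patient is missing from the secondary safety tables if the sequential scheme is carried into expansion and, on the literal reading, from the phase I DLT evaluation. Removing these patients can only bias toward safe.

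The conclusion about the definitions needs no numerical assumption. The size does: with replacement and an assumed share of 5% to 30%, the chance of passing rises from 53% to about 56% to 71% at a true DLT rate of 30%, and from 30% to about 33% to 49% at 40%. These figures illustrate the mechanism and are not estimates for this trial. The stronger statement, that the sequential scheme will look safer than it is, does not follow, because the article does not show that any such patient will occur.

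The wording should still be settled before the DLT decision is made, since that decision rests on 6 to 9 patients and can turn on one.

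**What to change.** Define the safety population as all patients who received any study treatment, meaning at least one SBRT fraction or at least one dose of either antibody. State that a DLT in a patient who has not received all components counts in the 6 or 9, and that only patients who are non-evaluable for reasons other than toxicity may be replaced. Name this population in the decision rule and in the phase I adverse event listing, so that they agree with the section on analysis of endpoints. Patients who received both components can be reported as a supplementary subset.

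The cost is a few sentences and no new data. Reported toxicity rates may be slightly less favourable.

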#### Statistical analysis of endpoints

The primary endpoint will be evaluated in the safety population. Secondary efficacy endpoints will be evaluated in the mITT population, and secondary safety endpoints in the safety population.

##### **Phase I**

The number of toxicities will be described by type and grade for each level (sequential and concomitant) according to the MedDRA classification. A listing of adverse events by patient and level will be provided.

##### Expansion cohort

Each cohort will be analyzed separately. PFS and OS rates (at 6 and 12 months) and median PFS and their respective 95% CI will be determined using the Kaplan-Meier method to take censored data into account. Toxicities will be described by type and grade according to the MedDRA classification. In the event a patient experiences several toxicities of the same type, only the highest grade will be retained for analysis. A listing of adverse events by patient will be provided. Analyses will be performed using SAS 9.4 or a later version.

### Interim analysis

An Independent Data Monitoring Committee (IDMC) will be established for the trial. This IDMC will meet after the inclusion of 10 patients with 5 weeks of follow-up in each cohort to evaluate toxicities, except for the lung cancer cohort, which will be evaluated during phase I. Toxicities will be described by grade and type of toxicity for each patient, focusing on the same DLT as described for phase I. The purpose of this interim analysis is to validate with the IDMC the safety of the combination of immunotherapy and radiation. Inclusion will be stopped while waiting for the IDMC meeting and decision. No interim analysis is planned for efficacy.

### Ethical and regulatory requirements

The study will be performed in accordance with ethical principles that have their origin in the Declaration of Helsinki, including Decree No. 2016 − 1537 of November 16, 2016 on research involving human subjects, and are consistent with ICH/Good Clinical Practice, and applicable regulatory requirements Patient Data Protection; in France, CNIL.

Before carrying out research on humans, the sponsor is required to submit the project to the opinion of one of the competent institutional ethical committees (Committee for the Protection of Persons: CPP) and to the regulatory authority (National Agency for the Safety of Medicines and Health Products: ANSM).

Prior to the implementation of the research on a person, the eligible subject will be fully informed by the investigator during the consultation, and after a period of reflection, a written informed consent form will be collected.

The information will also include information on data handling in accordance with the revised French Data Protection regulations including the European General Data Protection Regulation N° 2016/679.

